| **Study Design:** | Five doctors ([name], [name] [name], [name], [name]) will be hired to conduct a survey among  women visiting gynecological clinics. The doctors will have training from research team and from TRAINING AND RESOURCES IN RESEARCH ETHICS EVALUATION. The doctors will be trained how to recruit the participants and how to conduct a survey, and how to store completed questionnaires.  At the end of the appointment doctors will propose their patients to participate in the study.  Before participating in the survey prospective respondents will be provided information about research and doctors will read them verbal consent. Verbal consent will be used in the study.  Particularly for this research verbal consent will be used as way to receive informed consent from a participant. As anonymity of the study participants is our primary concern, verbal consent is deemed as most appropriate. Moreover, no personal information related to any of the patients will be made available to the Investigators at any time before, during or after the study. All the information about the study and participants rights will be stated both orally and on the information letter provided to the participants.  Once the respondent agrees to participate in the study, paper based questionnaires will be given to patients. There will be two types of questionnaires utilized to collect data on patient’s medical gynecological history and awareness and knowledge of HPV, and awareness of HPV vaccination. The first questionnaire will be filled out by doctors and consist of 30 items and include the following patient information: socio-demographic characteristics, lifestyle characteristics, and the history of gynecological diseases. The second questionnaire will be filled out by the respondents. The patient questionnaire will consist of 25 items and include the following information about the patients: socio-demographic characteristics, awareness of cervical cancer and the associated risk factors, awareness of screening for cervical cancer, whether the patient had gone through screening for cervical cancer, awareness of HPV, awareness of risks of HPV, and awareness of HPV vaccine.  Doctors and patients will fill out the questionnaires right after the appointment. For doctors it will take approximately 5 mins to complete the questionnaire. For patients it will take approximately 15 minutes to complete the questionnaire.  To keep anonymity survey respondents will be given IDs. Respondent ID will be written on both questionnaires.  Once completed the respondents will return completed survey to the doctor. The doctor will keep two questionnaires of each respondent in a closed box and only doctor will have access to the questionnaires.  Once doctor will gather 30-40 questionnaires, they will be sent to Nur-Sultan for further analysis and storage. An assigned courier will deliver questionnaire from each city to Nur-Sultan. Questionnaires will be delivered in a sealed folder.  Once questionnaires will be delivered to Nur-Sultan, they will be stored in closed box in PI’s office.  Only complete questionnaires with proper respondent ID will be analyzed for this study.  Data from paper-based questionnaires will be uploaded to computer with the use of Excel software. Once all questionnaires will be uploaded to Excel sheet, data will be imported into STATA16 software and further analyzed. |

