| **Inclusion Criteria:** | Women aged between 18 and 70 attending gynecological clinics, and living in one of the cities: Nur-Sultan, Almaty, Aktobe, Oskemen, Pavlodar will be included in the study |
| **Exclusion Criteria:** | Women outside of the age range (18-70) will be excluded from the study |
| **Number of Subjects:** | Approximately 2000 patients will be included in the study. Every doctor will collect around 400 surveys. |
| **Rationale for Number of Subjects:** | The number of patients can be explained by the budget provided to the doctors who will conduct the survey. Each doctor will be paid salary for conducting a survey. |
| **Study Duration:** | The study will be conducted between April 2019 and December 2020. |
| **Risks:** | It is possible that study participants may not:  -feel encouraged to share accurate and honest answers  -feel comfortable providing answers that present themselves in a unfavorable manner  -fully be aware of their reasons for any given answer because of lack of memory and knowledge on the subject |
| **Risk Mitigation:** | In order to avoid the risks outlined above subjects may skip any question they do not wish to answer and/or may withdraw consent from the study at any time without repercussion. |
| **Statistics:** | Statistical analysis will be performed using STATA 16 software. Data analysis will include descriptive statistics consisting of mean values, standard deviations, and frequencies, where applicable. Relationships between categorical variables will be analyzed using Chi-square test with significance value of <0.005. Crude odds' ratio (COR) and adjusted odds ratio (AOR) with 95% corresponding confidence intervals will be calculated in univariate and multivariable logistic regression models. A significance value <0.05 will be used as an indication of association between variables. |

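### The patient's completed form goes back to her treating doctor with no stated shielding of the answers, and the listed mitigations do not address the accuracy risk that the protocol names

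*Protocol*

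**What the plan says.** All of this is in the Protocol.

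- **Recruitment (Study Design row).** "At the end of the appointment doctors will propose their patients to participate in the study". The same doctor reads out the consent.
- **Completion (Study Design row).** The doctor fills in a 30-item form. Of the 25-item patient form it says: "The second questionnaire will be filled out by the respondents". On timing: "Doctors and patients will fill out the questionnaires right after the appointment".
- **Return and storage (Study Design row).** "Once completed the respondents will return completed survey to the doctor". Then: "The doctor will keep two questionnaires of each respondent in a closed box and only doctor will have access to the questionnaires". Both forms carry the same respondent ID. The only sealing mentioned is the courier's folder, used once the doctor has gathered a batch of 30 to 40.
- **Confidentiality (Study Design row).** Anonymity is described as the primary concern. The measures are IDs, verbal consent, and a statement that the Investigators receive no personal information.
- **Risks row.** Three risks are listed, without ranking. One is that women may not give accurate and honest answers. Another is that they may not "feel comfortable providing answers that present themselves in a unfavorable manner". The third concerns limited memory and knowledge.
- **Risk Mitigation row.** "In order to avoid the risks outlined above subjects may skip any question they do not wish to answer". The same sentence adds withdrawal of consent at any time.
- **Completeness (Study Design row).** Only complete forms with a proper ID are analysed. Complete is not defined.
- **Outcomes (Primary Endpoint row).** All three are patient answers: one Yes/No ever-heard item and two True/False statements.

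**The concern.** The protocol recognises that women may shade their answers, then routes those answers to the person before whom they are most likely to do so. A woman who has just been examined, and who expects her doctor to read the form, has a reason not to admit that she has never heard of something. The stated mitigation changes which answers are given, not how accurate the given ones are.

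The primary outcomes are at stake. All three rest on the patient form, and reporting bias does not shrink as the sample grows. A second problem follows from the mitigation itself: a woman who uses her permission to skip may be dropped from the analysis. If women who do not know the answer skip more often, dropping them would also push estimated awareness upward.

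**Working it through.** **Step 1: does any stated measure keep the answers from the doctor?**

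| Measure | Where | Hides answers from the doctor? |
|---|---|---|
| Self-completion | Study Design | No, the form is then returned to the doctor |
| Respondent ID | Study Design | No, the doctor holds both forms with the same ID |
| No personal data to Investigators | Study Design | No, it concerns the Investigators |
| Closed box | Study Design | No, the doctor is the one with access |
| Sealed courier folder | Study Design | No, it applies after the doctor has held the forms |
| Skip or withdraw | Risk Mitigation | No, it turns an answer into a missing one |

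**Step 2: the plan's own figure.** Five doctors × about 400 surveys = 2000, which matches the stated number of subjects. That number is set by budget, and no target precision is given.

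**Step 3: illustration of size.** The protocol gives neither a prevalence nor a misreporting rate, so both are assumed. Let p be true awareness and f the share of unaware women who answer yes.

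- Reported awareness = p + f(1 − p), so bias = f(1 − p).
- 95% half-width = 1.96 × √(p(1 − p)/n).

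For p = 0.40 and n = 2000, the half-width is 1.96 × √(0.40 × 0.60/2000) = 0.0215, about 2.1 points.

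- f = 2%: 0.40 + 0.02 × 0.60 = 0.412, bias 1.2 points (below sampling error).
- f = 5%: 0.40 + 0.05 × 0.60 = 0.430, bias 3.0 points (above).
- f = 10%: 0.40 + 0.10 × 0.60 = 0.460, bias 6.0 points (above).

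Bias and sampling error are equal at f = 0.0215/0.60 = 3.6%.

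Other assumed values of p, in percentage points:

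| True awareness | Half-width | Bias, f = 2% | Bias, f = 5% | Bias, f = 10% |
|---|---|---|---|---|
| 30% | 2.0 | 1.4 | 3.5 | 7.0 |
| 50% | 2.2 | 1.0 | 2.5 | 5.0 |
| 70% | 2.0 | 0.6 | 1.5 | 3.0 |

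At 10% the bias exceeds sampling error throughout. At 5% it does so at 30% and 50% but not at 70%. At 2% it never does.

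**Step 4: skipping against the complete-forms rule.** Suppose complete means that none of the 25 patient items is skipped, and that each is skipped independently with probability m (both assumptions). The share retained is (1 − m)^25.

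- m = 0.5%: 0.995^25 = 0.88, about 12% of forms lost.
- m = 1%: 0.99^25 = 0.778, about 22% lost (1556 of 2000 kept).
- m = 2%: 0.98^25 = 0.603, about 40% lost (1207 kept).

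If only the three outcome items had to be answered, 0.99^3 = 0.970 and 0.98^3 = 0.941 would be kept at m = 1% and 2%. The loss therefore depends strongly on what complete means.

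**The case against.** The strongest reply is that this is a choice of procedure, not an error. The form is self-completed, carries no name, and is collected by doctors trained in conducting surveys and storing the forms. The doctor must know which ID belongs to which woman, because the design links two forms. The anonymity text refers to the Investigators and never promises that the doctor cannot recognise the patient. Much of this stands: the face-to-ID link is inherent, and the point is limited to the doctor's ability to see her 25 answers.

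A reader might also infer several stronger things that the protocol does not support:

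- **That the form is handed over open.** The protocol is silent on whether it is folded, covered or sealed. What can be said is that no shielding is described.
- **That dishonest answers are the main risk, or that skipping is the only mitigation.** The risks are unranked, and withdrawal is offered too.
- **That all awareness items are biased upward.** The over-reporting model fits the ever-heard item best. For a True/False statement, a wish to please does not tell the woman which answer is right.
- **That the bias differs by doctor and distorts clinic comparisons.** It may differ, but nothing in the protocol shows this, and the Statistics row specifies no clinic comparison.

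The conflict between skipping and the complete-forms rule would exist whoever collected the form. It belongs here because the protocol presents skipping as the remedy for the accuracy risks.

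**Conclusion.** The point holds in a limited form. The treating doctor receives and holds the patient's answers with no stated shielding. The protocol names inaccurate and face-saving answers as two of three risks, and skipping or withdrawing does not make given answers more accurate. The permission to skip and the complete-forms rule pull against each other and must be reconciled.

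The size is unknown. At an assumed true awareness of 40%, the bias passes the sampling error of about 2.1 points once roughly 3.6% of unaware women over-report. Below that it is the smaller of the two. This rests on assumed rates, on misreporting in one direction only, and on simple random sampling for the half-width. It applies most clearly to the ever-heard item. The change is worth making because it is cheap and protects the primary outcomes, not because bias has been shown.

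**What to change.** 1. The patient seals her own form in an envelope marked only with the respondent ID. Alternatively, she posts it in a locked box to which the doctor has no key. The existing box would not serve, since at present "only doctor will have access to the questionnaires".
2. The doctor stores the doctor form separately under the same ID, which keeps the linkage.
3. Only the research team in Nur-Sultan opens the envelopes, and the information letter tells the woman so before she answers.
4. The access sentence in the Study Design row and the Risk Mitigation row are rewritten to match. Skipping and withdrawal remain as participant rights but are no longer presented as the remedy for inaccurate answers.
5. The complete-forms rule is replaced by analysis of the available answers for each outcome, with the number analysed reported for each.

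The cost is envelopes (or separate boxes) and a few sentences in the protocol and information letter. The real downside is that the doctor can no longer check the patient form for completeness on site. Some forms will then arrive with gaps, which is why the fifth change has to accompany the first. Adjusted models will still lose women with missing covariates.

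### The analysis is limited to complete questionnaires, with 'complete' undefined, although women may skip any question; a blank unrelated to any outcome could remove a woman from every analysis

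*Protocol*

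**What the plan says.** The protocol sets the analysis set under Study Design: "Only complete questionnaires with proper respondent ID will be analyzed for this study". The ID is what links the two forms kept for each woman. One is completed by the doctor ("The first questionnaire will be filled out by doctors and consist of 30 items") and the other by the woman herself ("The patient questionnaire will consist of 25 items").

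Under Risk Mitigation it says that "subjects may skip any question they do not wish to answer and/or may withdraw consent from the study at any time without repercussion". This is the response to the concerns listed under Risks, which include reluctance to give answers that reflect badly on the respondent, and limited recall or knowledge of the topic.

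On size, Number of Subjects says: "Approximately 2000 patients will be included in the study. Every doctor will collect around 400 surveys". The rationale for that number is budgetary, and no allowance for incomplete forms is mentioned. Primary Endpoint shows the three outcomes with two response options each (Yes/No or True/False).

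The protocol does not say what makes a questionnaire complete. It gives no expected skip rate, and its only handling of partly answered forms is to leave them out.

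**The concern.** The two provisions work against each other. A woman who uses the permission to skip produces a form that, on the plain reading, is not complete. She then drops out of every prevalence estimate and every logistic model, including those for which she supplied all the data needed.

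Two things are at stake. The first is lost data: the number analysed could fall well short of the number collected. The second is selection. The outcomes are awareness and knowledge, and the protocol itself foresees lack of knowledge as a source of poor answers. If women who know less leave more blanks, those retained will look better informed than those surveyed, and a larger sample would not correct that.

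The undefined term adds a further problem: the boundary of the analysis set could be drawn after the data have been seen.

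**Working it through.** **Planned number.** Five doctors (Study Design) at about 400 surveys each (Number of Subjects) give 5 × 400 = 2,000, which agrees with the stated total. This is the number collected; the number analysed is not stated.

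**Loss under the literal rule.** Let s be the chance that a woman skips any one item. The protocol gives no value, so s is assumed. With independent skipping over the k = 25 items of the patient form, the share of complete forms is (1 − s)^25.

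| s per item | (1 − s)^25 | kept of 2,000 | lost |
|---|---|---|---|
| 0.1% | 0.975 | 1,951 | 49 (about 2.5%) |
| 0.5% | 0.882 | 1,764 | 236 (12%) |
| 1% | 0.778 | 1,556 | 444 (22%) |
| 2% | 0.603 | 1,207 | 793 (40%) |

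If blanks cluster in the same women, fewer forms are lost at the same s. Under per-item inclusion, a one-item prevalence at s = 1% would use 2,000 × 0.99 = 1,980 women, which is 1,980 − 1,556 = 424 more.

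**Precision.** The 95% half-width for a prevalence of 50%, treating the sample as simple random, is 1.96 × √(0.25/n): 2.2 points at n = 2,000, 2.5 at 1,556 and 2.8 at 1,207. The loss of precision is real but modest.

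**Bias in prevalence.** With true prevalence p and completion rates ca (aware) and cu (unaware), the reported value is p·ca / [p·ca + (1 − p)·cu]. The completion rates below are assumed, with p = 50%:

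- 90% in both groups: no bias.
- 95% aware, 85% unaware: 52.8%, or +2.8 points.
- 90% aware, 70% unaware: 56.2%, or +6.2 points.
- 70% aware, 90% unaware: 43.7%, or −6.3 points.

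A moderate difference in completion can therefore exceed the sampling error, in either direction.

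**How much of this the rule itself causes.** Suppose aware women skip 0.5% of items and unaware women 1%, with p = 50%. Whole-form completion is 0.995^25 = 0.882 and 0.99^25 = 0.778, and the reported value is 0.882 / (0.882 + 0.778) = 53.1%. Using everyone who answered the single outcome item gives 0.995 / (0.995 + 0.990) = 50.1%. Here per-item inclusion removes nearly all of the bias.

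Suppose instead that the blank is on the outcome item itself: p = 40%, skipped by 2% of women who know and 20% of those who do not. Among answerers the result is 0.40 × 0.98 / (0.40 × 0.98 + 0.60 × 0.80) = 0.392 / 0.872 = 45%. Dropping the complete-form rule does not change this. Counting blanks as not knowing gives 0.392 / 1 = 39.2%.

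**Odds ratios.** If completeness depends only on the outcome, the factor ca/cu multiplies the odds at every level of a factor and cancels in the odds ratio. If it depends only on covariates in a correctly specified model, the complete-case odds ratio is also unbiased. Bias needs joint dependence on outcome and factor, for example if not knowing leads to blanks more often among less-educated women than among others.

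**The case against.** The strongest reply is that the rule may not mean that every item must be answered. Elsewhere in Study Design, completed forms are simply forms that have been filled in and handed back, and the rule names the ID that links the pair. It could mean only that both forms were returned and can be matched. That reading is possible, so exclusion for one blank is a consequence of the literal reading and not a settled fact. It does not rescue the text, which must say which meaning applies.

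A reader might infer that a large part of the sample will be discarded. The documents do not support this, because no skip rate is given and the assumed range above runs from about 2.5% to 40%. Requiring all 30 + 25 = 55 items at 1% skipping would keep only 1,151 women. But that applies the patient's rate to 30 items filled in by doctors, whereas the skip permission is given to subjects.

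A reader might also infer that awareness will certainly be overstated. That is plausible but not shown. For the question on having heard of the vaccine, an unaware woman can simply answer No; on a True/False item she may guess. Women may also skip personal items for reasons unrelated to knowledge, so the bias could be nil or reversed.

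Nor does it follow that associations are biased for any factor related to skipping; the condition is the narrower one given above. The 45% example illustrates skipping of the outcome item and cannot be charged to the complete-form rule. Skipping is also not the only mitigation offered, since consent may be withdrawn.

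Finally, the imputation method can properly be left to a statistical analysis plan. The analysis-set rule is different, because the protocol itself fixes it.

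**Conclusion.** The concern stands as a conflict between the analysis-set rule and the permission to skip, made worse by an undefined term. On the plain reading, women who supplied every outcome are excluded for unrelated blanks, which wastes data that have been collected.

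The size is conditional: about 2.5% to 40% of 2,000 lost for assumed skip rates of 0.1% to 2% per item, with independence over the 25 items, and less if skips cluster. Upward bias in prevalence is the likelier direction if women who know less skip more, but neither its presence nor its size can be established from the protocol. Odds ratios are at risk only under joint dependence of completeness on outcome and factor. The text should be amended because the rule governs all three outcomes and every model.

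**What to change.** Replace the sentence in Study Design with a rule along these lines: *all consented questionnaire pairs with a valid matching ID are analysed; each prevalence uses all women who answered that outcome item; each model uses all women with the outcome and the covariates it needs, or with imputed covariates.* If the word complete is kept anywhere, define it.

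State how blank outcome items are coded. Report each prevalence a second time with blanks counted as not aware or not knowing, since the analysis among answerers cannot address skipping of the outcome item itself. Report the numbers collected, analysed and missing for each item, so that 2,000 collected is not read as 2,000 analysed.

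This needs a short protocol amendment and no new data. The cost is a little more analysis work and denominators that differ between analyses.

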**Survey Protocol**

| **Protocol Title:** | Survey protocol for the study called : **Knowledge and awareness of human papillomavirus infection and human papillomavirus vaccine among Kazakhstani women attending gynecological clinics** |
| --- | --- |
| **Institution/Affiliation:** | Nazarbayev University  <https://nu.edu.kz/> |
| **Principal Investigator Name/Contact Information:** | [name]  [[contact]](mailto:[contact]) |
| **Sub Investigator(s) Name/Email:** | [name] [contact]  [name] [contact]  [name] [contact]  [name] [contact]  [name] [contact]  [name] [contact]  [name] [[contact]](mailto:[contact]) |
| **Study Contact Person Name/Email:** | [name]  [[contact]](mailto:[contact]) |
| **Locations of survey:** | Obstetrics and Gynecology Department, Keruen Medicus Clinic, Almaty 050040, Kazakhstan;  Obstetrics and Gynecology Department, East Kazakhstan Regional Hospital, Oskemen 07000, Kazakhstan;  Regional Perinatal Center, [name], Aktobe 030006, Kazakhstan;  Obstetrics and Gynecology Department, City polyclinic #6, Nur-Sultan 010000, Kazakhstan;  Gynecology Department, Daliya Clinic, Pavlodar 140013, Kazakhstan |
| **Rationale:** | Although cervical cancer remains one of the top causes of cancer-related morbidity and mortality all over the world, there are no currently published studies to assess the knowledge of HPV and cervical cancer in Kazakhstan. |
| **Primary Objectives:** | The aim of this study is to assess the awareness about HPV, the knowledge of HPV as a cause of cervical cancer, and the awareness of HPV vaccination among Kazakhstani women visiting gynecological clinics in five different parts of the country and to identify the factors associated with the awareness of HPV and HPV vaccine, and knowledge of HPV as a major cause of cervical cancer. |
| **Primary Endpoint:** | Outcome variables for this study are the following: awareness of HPV (“Have you ever heard about HPV vaccine?” Yes/No); knowledge of HPV as a major cause of cervical cancer (“HPV infection is the major cause of cervical cancer.” True/False); awareness of HPV vaccine (“There is a vaccine against HPV infection.” True/False). |

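### The Statistics row sets two conflicting significance thresholds for association: <0.005 for chi-square and <0.05 for association between variables

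*Protocol*

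**What the plan says.** The Primary Objectives row includes the aim "to identify the factors associated with the awareness of HPV and HPV vaccine, and knowledge of HPV as a major cause of cervical cancer". The Primary Endpoint row defines three outcomes, each answered Yes/No or True/False.

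The Statistics row then takes three steps:

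- Chi-square: "Relationships between categorical variables will be analyzed using Chi-square test with significance value of <0.005".
- Logistic regression: crude odds ratios and "adjusted odds ratio (AOR) with 95% corresponding confidence intervals will be calculated in univariate and multivariable logistic regression models".
- A closing rule: "A significance value <0.05 will be used as an indication of association between variables".

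The row mentions no multiplicity correction or screening step that would explain a stricter chi-square level. On size, the protocol says "Approximately 2000 patients will be included in the study. Every doctor will collect around 400 surveys", and the Rationale for Number of Subjects row bases this on the survey budget, not on a power calculation. No alpha level is fixed there either.

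**The concern.** The two thresholds differ ten-fold and apply to overlapping questions. If the closing rule covers only the regression models, chi-square and the crude odds ratio can return opposite verdicts on the same table. If it covers association in general, as its wording allows, it contradicts the chi-square sentence directly. The conflict exists on either reading.

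At stake is how the second half of the primary objective is reported. A factor in the gap could appear as non-significant in a chi-square table and as associated in the odds ratio table of the same report, and the protocol does not explain what the stricter verdict is for.

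**Working it through.** **Inputs from the protocol.** Chi-square threshold 0.005, association threshold 0.05 and confidence level 95% (Statistics row); binary outcomes (Primary Endpoint row); about 2000 women, which agrees with 5 doctors × 400 surveys = 2000 (Study Design and Number of Subjects rows).

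**Assumptions, not in the protocol.** A two-level factor splitting the sample 1000/1000, 40% awareness in the reference group, and a range of true odds ratios.

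**1. Which threshold fits the intervals.** The thresholds are chosen settings, so there is no derivation to reproduce, but consistency can be checked. 1 − 0.95 = 0.05, so the planned intervals match 0.05. A 0.005 level would pair with 1 − 0.005 = 99.5% intervals. The two-sided critical values are z = 1.960 (chi-square 3.84 on 1 df) and z = 2.807 (chi-square 7.88).

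**2. One table, two verdicts.** Take 400/1000 aware versus 450/1000 aware.

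- Pearson chi-square = 2000 × (400×550 − 450×600)² / (1000×1000×850×1150) = 5.12, p = 0.0237 (0.0267 with continuity correction). This is below 7.88, so not significant at 0.005.
- Crude odds ratio = (450×600)/(550×400) = 1.227; log = 0.2048.
- Standard error = √(1/450 + 1/550 + 1/400 + 1/600) = 0.0906; z = 0.2048/0.0906 = 2.26; Wald p = 0.0238.
- 95% CI = exp(0.2048 ± 1.960×0.0906) = 1.03 to 1.47, so associated at 0.05.
- 99.5% CI = exp(0.2048 ± 2.807×0.0906) = 0.95 to 1.58, which includes 1 and would agree with the 0.005 verdict.

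The p-values agree to three decimals (0.024). The thresholds alone cause the disagreement.

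**3. How often this happens.** With p₁ = odds/(1 + odds), where odds = (0.4/0.6) × OR, p̄ the mean of p₁ and 0.4, and z = (p₁ − 0.4)/√(2p̄(1 − p̄)/1000), power at critical value c is Φ(z − c) + Φ(−z − c). The chance of conflict is power at 1.960 minus power at 2.807.

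| True OR | p₁ | z | Power at 0.05 | Power at 0.005 | Conflict |
|---|---|---|---|---|---|
| 1.0 | 0.400 | 0 | 0.050 | 0.005 | 4.5% |
| 1.1 | 0.423 | 1.05 | 0.182 | 0.039 | 14% |
| 1.25 | 0.455 | 2.47 | 0.693 | 0.366 | 33% |
| 1.3 | 0.464 | 2.90 | 0.827 | 0.538 | 29% |
| 1.5 | 0.500 | 4.49 | 0.994 | 0.954 | 4% |
| 1.7 | 0.531 | 5.88 | >0.999 | 0.999 | 0.1% |

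The difference peaks at z = (1.960 + 2.807)/2 = 2.38, where it is about 33%. An odds ratio of 1.25 under these assumptions is practically at that ceiling. With a 400/1600 split, an odds ratio of 1.5 gives about 16% instead of 4%.

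**4. Which observed differences are affected.** With 2000 women, base rates of 30% or 50%, and splits of 1000/1000 or 400/1600, the conflict zone begins at a difference of 4.1 to 5.5 percentage points and ends at 6.0 to 7.8 points.

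**The case against.** **The closing sentence may govern.** It uses the same notion of association as the objective, is worded generally, and follows the regression models and their 95% intervals. The natural reading is that association is declared at 0.05. This has force: a reader might infer that the analyst is free to pick a verdict after seeing the data, and the text does not go that far. But the chi-square sentence still carries its own significance value with no stated role, so the conflict remains.

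**The tests are not always equivalent.** This stands. For a multi-level factor such as city, with five sites, chi-square is one omnibus test, while odds ratios are usually given level by level against a reference. Adjusted odds ratios answer a different question again. Both can legitimately differ from chi-square at a single threshold. A reader might infer that every factor with p between 0.005 and 0.05 must receive opposite verdicts. That follows only for two-level factors or joint tests of all levels.

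**The 0.005 is probably a slip.** The 95% intervals make that plausible. Equally, it could be an unstated correction, since 0.05/10 = 0.005. The protocol supports neither explicitly, so the document has to settle it.

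**A statistical analysis plan may cover it.** One may exist, but this is not an omitted detail: the protocol states two incompatible values.

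**Conclusion.** The contradiction is real, and it touches the rule for declaring association under a primary objective. It should be fixed, but its reach is limited. Estimates and confidence intervals do not change, and the sample size was set by budget, so it does not depend on alpha. Only the label attached to a factor is affected.

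Under the assumed 40% baseline and 1000 per group, the chance of conflicting verdicts runs from near 0 to about 33%, depending on the true effect. A reader might take a figure near 30% as typical. It is close to the mathematical maximum and applies only to odds ratios of roughly 1.25 to 1.3 under these assumptions. With no association it is 4.5%, and for strong associations it is negligible.

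**What to change.** State one two-sided significance threshold for both the chi-square and the logistic regression results. A level of 0.05 matches the 95% intervals already planned and needs no other change.

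If 0.005 was intended, give the reason, say what role the chi-square verdict plays, and apply the same level to the logistic results with matching 99.5% intervals.

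The cost is one sentence in the Statistics row. No additional data or participants are needed.
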